#### Secondary outcomes

1. Complications (Clavien-Dindo classification), 30 days
2. Rate and severity of postoperative pancreatic fistula (ISGPS classification), 30 days
3. Rate and severity of delayed gastric emptying (ISGPS classification), 30 days
4. Rate and severity of post-pancreatectomy haemorrhage (ISGPS classification), 30 days
5. Length of hospital stay, days
6. Readmissions, 30 days
7. Number of patients received adjuvant therapy among patients with cancer diagnosis

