#### Tertiary outcomes

1. Overall survival, 1, 5, 10y
2. Disease-free survival, 1, 5, 10y
3. Disease-specific survival, 1, 5, 10y

Outcome measures will be analyzed in following subgroups: 1) Patients who have undergone pancreaticoduodenectomy, 2) Patients who have undergone distal resection

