## **Statistical analysis plan**

Non-inferiority will be tested by lower limit the mean difference's 90% confidence interval (equivalent of 95% confidence interval of one-sided test). If the lower limit of CCI's mean difference's 90% confidence interval is under -9, non-inferiority is not met. Of primary and secondary outcomes, CCI and length of stay will be presented as mean (standard deviation) and compared between groups using independent t-test with bootstrapping. Only primary outcome will be assessed using non-inferiority testing, and secondary outcomes will be assessed using superiority approach. Categorical secondary outcome measures are compared using Chi square test. Effect sizes are reported either as mean difference with 95% confidence interval or odd ratios (OR) with 95% confidence interval. All p-values reported are two-sided and for superiority testing. P-value <0.05 was considered statistically significant. Missing data, if any, will be reported. Missing data are omitted from analyses of the particular variable in question and no missing data is imputed. All outcomes will be analyzed using modified intention-to-treat analyses, where all randomized patients in whom the study drug is continued after surgery are included in the analyses. Subgroup analyses are performed using superiority testing for patients undergoing pancreaticoduodenectomy or distal pancreatectomy.

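### Procedure subgroups are tested separately for superiority at P<0.05, with no interaction test and no statement that unadjusted secondary and subgroup results are exploratory

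*Protocol*

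**What the plan says.** The Statistical analysis plan section gives the primary outcome, CCI at 30 days, its own framework and puts the other outcomes in a different one: "Only primary outcome will be assessed using non-inferiority testing, and secondary outcomes will be assessed using superiority approach". It then sets one rule for p-values, "All p-values reported are two-sided and for superiority testing", and one threshold, "P-value <0.05 was considered statistically significant". CCI is also compared between groups by t-test, so it too receives a superiority p-value.

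Secondary outcomes lists seven items. Three of them join rate and severity, for example "Rate and severity of postoperative pancreatic fistula (ISGPS classification), 30 days".

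The subgroup rule appears twice. The text after Tertiary outcomes says "Outcome measures will be analyzed in following subgroups" and names pancreaticoduodenectomy and distal resection. The Statistical analysis plan section says "Subgroup analyses are performed using superiority testing for patients undergoing pancreaticoduodenectomy or distal pancreatectomy".

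The protocol contains no interaction test, no order of testing among the superiority comparisons, no adjustment for their number, and no statement that secondary or subgroup results are exploratory.

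**The concern.** There are two separate problems.

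The first is the subgroup method. The natural question about the two procedures is whether the choice of drug matters more in one than in the other. A test inside each procedure does not answer it. The subgroups differ in size and so in power, and one can cross P<0.05 while the other does not when the drug effect is the same in both. Under the stated rule, that pattern would be reported as a significant difference in one procedure only.

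The second is how many p-values share the one threshold. Each superiority test carries a 5% chance of a false positive, and each is to be called statistically significant on its own. The Hypothesis section names fistula alongside complications, but fistula is only a secondary outcome. A chance result on fistula, haemorrhage, stay or readmission, overall or in one procedure, would therefore be published beside the non-inferiority result and described as significant, with nothing in the plan to tell the reader how much weight it bears.

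**Working it through.** **Inputs from the protocol.** Seven secondary outcomes; a CCI superiority t-test; two procedure subgroups plus the whole sample; two-sided 0.05; margin 9, SD 20, 62 per group (Sample size); a one-sided 5% non-inferiority test, through the 90% confidence interval.

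**Assumptions, because the protocol gives no figures.** Procedure shares of 60% pancreaticoduodenectomy, 30% distal and 10% other, varied to 50/40 and 70/25; correlation between outcomes from 0 to 0.8; event rates of 8-30% for the complication and readmission outcomes; chi-square with or without continuity correction.

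**1. The plan's own figure.** n per group = 2 × (1.645 + 0.842)² × 20² / 9² = 61.06, rounded up to 62. This matches, with 80% power assumed because none is stated. The trial is sized on the CCI non-inferiority test alone. That is one test, so the number of superiority tests does not change its error rate.

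**2. Number of superiority tests.** 7 secondary outcomes + CCI = 8; 8 × 3 populations = 24. Testing rate and severity separately, and the three survival outcomes at three time points, would add more.

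**3. Subgroup tests when the true effect is identical.** With 80% overall power, two-sided 0.05, the expected z is 1.96 + 0.842 = 2.802. In a subgroup with share s it is 2.802 × √s.
- Share 60%: 2.802 × √0.6 = 2.17; power = Φ(2.17 − 1.96) = 0.58.
- Share 30%: 2.802 × √0.3 = 1.53; power = Φ(1.53 − 1.96) = 0.33.
- One significant and the other not: 0.58 × 0.67 + 0.42 × 0.33 = 0.53.

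Shares of 50/40 give 0.50, and 70/25 give 0.56. The result also depends on overall power: with 60/30 shares it is 0.39 at 50% power and 0.53 at 90%.

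**4. Chance of at least one P<0.05 when no outcome truly differs.** With independent tests, 1 − 0.95⁷ = 0.302 for the seven secondary outcomes and 1 − 0.95²⁴ = 0.708 for 24. The second figure is too high, because each subgroup is part of the whole sample and the outcomes are related. The whole-sample z was therefore built as the share-weighted sum of independent subgroup z-values, with equal correlation between outcomes (200,000 simulated trials, 60/30/10 shares):

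| Outcome correlation | 7 secondaries, whole sample | 24 tests |
|---|---|---|
| 0 | 0.30 | 0.63 |
| 0.3 | 0.27 | 0.58 |
| 0.5 | 0.23 | 0.50 |
| 0.7 | 0.18 | 0.40 |
| 0.8 | 0.15 | 0.33 |

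The other shares move the 24-test figure by about one percentage point. A patient-level simulation with 62 per arm, t-tests and chi-square tests gives, for 24 tests, 54-63% with uncorrected chi-square and 35-44% with continuity correction. For the seven secondary outcomes alone it gives 25-30% and 17-20%.

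**5. What an interaction test can detect for CCI at 124 patients (SD 20, 60/30 shares).** Subgroup sizes are 74.4 and 37.2. The standard error of each drug difference is 20 × √(4/74.4) = 4.64 and 20 × √(4/37.2) = 6.56. The standard error of their difference is √(4.64² + 6.56²) = 8.03. A difference between procedures of 2.802 × 8.03 = 22.5 CCI points is needed for 80% power; for one of 9 points, power is about 20%.

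**The case against.** The strongest reply is that the decision is already protected. There is one primary outcome, the trial is sized on it, and it alone is tested for non-inferiority. Unadjusted secondary p-values beside a single primary are common practice, and multiplicity handling often sits in a separate statistical analysis plan. The protocol also already commits to effect sizes with 95% confidence intervals.

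Most of this stands, and it limits the point. A reader might infer that a chance secondary result could override the non-inferiority conclusion. Nothing in the protocol allows that. A reader might also infer that the outcomes have no hierarchy. They are ranked primary, secondary and tertiary; what is absent is any effect of that ranking on how a superiority p-value is read. Formal error control across the secondary outcomes is a trade-off, and leaving it out is not in itself an error.

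The size also needs care. Correlation between outcomes could be high: CCI is built from Clavien-Dindo grades, and fistula, gastric emptying and haemorrhage are coded among those graded complications. Chi-square tests in a small distal subgroup can reject less often than 5% when events are rare. Both push the 24-test figure towards its lower end.

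The reply that this is only missing detail does not stand. The protocol has its own analysis section, which fixes the 0.05 rule for every reported p-value and prescribes superiority testing inside each procedure. That is a stated method, and it is the wrong one for asking whether the effect differs by procedure.

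**Conclusion.** The point holds in a limited form. Its firmest part is the subgroup method: separate tests cannot establish a procedure-specific drug effect, and with an identical true effect they disagree about half the time (50-56% over the shares tried, at 80% overall power). The logical flaw does not depend on those assumptions; only its frequency does.

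The second part concerns interpretation. If the drugs differ on no outcome, at least one P<0.05 is expected in about 15-30% of trials for the seven secondary outcomes in the whole sample, and in about one-third to 63% for all 24 tests. Correlation, event rates, procedure shares and the version of chi-square are assumed. It is tempting to say that a false claim is about as likely as not. That describes only the pooled 24-test family in the middle of its range, and it does not describe the secondary outcomes in the whole sample.

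The primary CCI non-inferiority test, the sample size and the data collection are unaffected.

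**What to change.** In the Statistical analysis plan section:

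1. Replace the separate superiority tests within procedures by a treatment-by-procedure interaction test, at least for CCI and fistula. Show the drug difference in each procedure with its 95% confidence interval, descriptively.
2. State that CCI non-inferiority is the only confirmatory test, that CCI superiority is tested only once non-inferiority is met, and that p-values for secondary, tertiary and subgroup results are unadjusted and exploratory.

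A Holm procedure or a fixed sequence across the secondary outcomes is an option if the sponsor wants to make claims on them; it is not required.

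The cost is wording and an interaction term in the model. No patients or data are added. There are two drawbacks. Secondary and subgroup differences can no longer be presented as confirmed on an unadjusted P<0.05. The interaction tests have low power at 124 patients, so a non-significant interaction should not be read as proof of equal effects.

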**Criteria to remove patients from analyses after randomization:**

- Pancreatic resection was not performed (e.g. disseminated cancer)
  - Hard pancreas and/or dilated pancreatic duct (so called low risk pancreas) (applies only to patients undergoing pancreaticoduodenectomy – the decision is made intraoperatively)
  - Patient withdraws consent (data collected until withdrawal will be used in the study)
- NOTE! Unmasking or premature stopping of the trial drug will not remove patient from the trial.

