## **References**

Laaninen M, Sand J, Vasama K, Laukkarinen J. Whipplen leikkauksen jälkeisiä komplikaatioita voidaan vähentää hydrokortisonihoidolla. *Randomoitu*

plasebokontrolloitu tutkimus. Suomen Kirurgiyhdistys ry 2015 36;4

Collected parameters

Name

Social security number

Date of birth

Gender (1 = male, 2 = female)

Charlson comorbidity index

Medication

Anticoagulation (0 = no, 1 = yes)

Immunosuppression (0 = no, 1 = yes)

Cortisone (0 = no, 1 = yes)

Date of diagnosis of pancreatic tumor (suspicion) (=computed tomography date)

Preoperative diagnosis (1 = pancreatic cancer, 2 = cholangiocarcinoma, 3 = IPMN, 4 = NET, etc)

Neoadjuvant therapy (0 = no, 1 = gemcitabine, 2 = folfirinox, 4 = chemoradiotherapy, 4 = other)

Randomization group (1 = signifor, 2 = cortisone)

Date of surgery

Type of surgery (1 = whipple, 2 = distal resection, 3 = enucleation, 4 = median pancreatectomy, 4 = exploration, 5 = total pancreatectomy, 6 = other)

Venous resection (0 = no, 1 = portal/SMV, tangential or end-to-end, 2 = porta/SMV,

Arterial resection (0 = no, 1 = yes)

Pancreaticojejunostomytype (1 = Heidelberg, 2 = [name], 3 = other)

Consistency of pancreas (1 = hard, 2 = soft, normal)

Pancreatic duct at operation (1 = small, normal, 2 = dilated)

Pancreatic duct size, computed tomography, mm

Drains (0 = no, 1 = one drain, 2 = two drains)

Was study drug continued after operation (1 = yes, 2 = no, hard pancreas/dilated duct in patient undergoing whipple, 3 = no, no operation, 4 = no, total pancreatectomy)

Complications, 30 days from operation

Pancreatic fistula, ISGPS grade

DGE, ISGPS grade

Postop haemorrhagia, ISGPS grade

First complication, C-D class

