### **Kriteerit poistaa potilas tutkimuksesta randomisaation jälkeen:**

- Haimaresektiota ei tehdäkään (esim. levinnyt syöpä)
- Haima on kova ja/tai haimatiehyt on laaja (ns. pienen riskin haima) (koskee vain potilaita, joille on tehty pankreatikoduodenektomia - päätös tehdään intraoperatiivisesti)
- Potilaalle tehdäänkin totaalipankreatektomia
- Potilas haluaa keskeyttää tutkimuksen (keskeyttämiseen mennessä kerättyjä tietoja käytetään tutkimuksessa).

HUOM! Sökkouttamisen purkaminen ja tutkimuslääkkeen ennenaikainen lopettaminen ei poista potilasta tutkimuksesta.

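### The analysis set is defined by whether study drug was continued after surgery, which conflicts with the protocol's own removal rules and should be restated in operative terms

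*Protocol*

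**What the plan says.** Three parts of the protocol decide who is analysed.

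- **Statistical analysis plan.** All outcomes, including the single non-inferiority test on CCI, use a modified intention-to-treat set in which "all randomized patients in whom the study drug is continued after surgery are included in the analyses".
- **Criteria to remove patients from analyses after randomization.** The English list names three grounds: no resection ("Pancreatic resection was not performed (e.g. disseminated cancer"), a low-risk pancreas found during pancreaticoduodenectomy, and withdrawn consent. A note adds: "Unmasking or premature stopping of the trial drug will not remove patient from the trial". The Finnish list has a further ground, that a total pancreatectomy was performed after all: "Potilaalle tehdäänkin totaalipankreatektomia".
- **Collected parameters (appendix 1).** The field on drug continuation has one code for yes and three for no. The first of these is a hard pancreas or dilated duct at a Whipple operation, and the other two are "3 = no, no operation, 4 = no, total pancreatectomy".

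Under Randomization, the allocated treatment starts before surgery. Whether it continues afterwards is therefore settled after both randomisation and first dose.

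**The concern.** Membership of a randomised comparison should not depend on an event that the treatment, or an early complication, can influence. Whether the drug is restarted after surgery can be such an event. The Blinding section lets doctors learn the allocation when they suspect an important adverse event or need to change treatment, so a decision not to restart could be made knowing the arm.

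The direction matters because the primary test is for non-inferiority. If patients who did badly were lost from the cortisone arm and not from the pasireotide arm, the cortisone mean would look better than it is and the error would favour the trial's hypothesis. The sections also disagree on who belongs in the set, so the choice could be made after outcomes are known.

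**Working it through.** **Step 1. Apply the rules to the patients in question.**

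| Patient | English removal list | Statistical analysis plan | Form code |
|---|---|---|---|
| No resection | removed | dropped | no operation |
| Low-risk pancreas at pancreaticoduodenectomy | removed | dropped | hard pancreas/dilated duct |
| Total pancreatectomy performed | kept (Finnish list: removed) | dropped | total pancreatectomy |
| Partial resection, not low-risk, some postoperative doses, then stopped | kept | kept on the natural reading | yes |
| Partial resection, not low-risk, never restarted (e.g. adverse event, early death) | kept | dropped if read literally | none |

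The sections disagree on the third and fifth rows. The third needs no assumption, because the form foresees that patient. The fifth depends on taking the analysis-set sentence literally.

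**Step 2. Reproduce the plan's own figure.** Under Sample size, the margin is 9 CCI points, the SD 20 and the size 62 per group. The Statistical analysis plan gives a 90% interval, that is one-sided 5%. Power is not stated; 80% is assumed.

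n = 2 × [20 × (1.645 + 0.842) / 9]² = 61.06, rounded up to 62 per group.

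The stated size reproduces, so the sample-size arithmetic is not in question. The standard error is 20 × √(2/62) = 3.592.

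**Step 3. Illustrate the literal reading.** Suppose a fraction f of the cortisone arm is dropped for non-operative reasons, and those patients have a mean CCI D points above the rest of their arm. Dropping them lowers the arm mean by f × D. Take a true cortisone excess of 9 points (the margin), 62 pasireotide patients, 62 × (1 − f) cortisone patients and SD still 20. Then

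SE = 20 × √(1/62 + 1/[62(1 − f)]), and false non-inferiority = Φ(f × D / SE − 1.645).

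| f | D | Shift f × D | SE | False non-inferiority |
|---|---|---|---|---|
| 0 | any | 0 | 3.592 | 5.0% |
| 2% | 20 | 0.4 | 3.610 | 6.3% |
| 2% | 40 | 0.8 | 3.610 | 7.7% |
| 5% | 20 | 1.0 | 3.639 | 8.5% |
| 5% | 40 | 2.0 | 3.639 | 13.7% |

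These fractions are 62 × 0.02 = 1.2 and 62 × 0.05 = 3.1 patients. Both f and D are assumptions; the documents give neither.

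**Step 4. Other directions.** If both arms lose the same fraction with the same D, the shifts cancel: f × D − f × D = 0. If only pasireotide loses patients, the sign reverses and the test becomes conservative. For f = 5% and D = 40 the error is Φ(−2.0/3.639 − 1.645) = Φ(−2.195), about 1.4%.

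**The case against.** The strongest reply is that the data form already settles what was meant. Its only codes for a drug not continued are operative, and they match the three operative grounds in the Finnish removal list. On that reading the analysis-set sentence abbreviates those removals, the note on premature stopping covers everyone else, and the missing code for other reasons shows that none was meant to exclude a patient. The low-risk decision is made during the operation by doctors who are meant to be unaware of allocation, so the main removals are not obviously related to arm.

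Much of this stands. A reader might infer that the plan sets out to exclude treatment failures, or that the false non-inferiority rate is in fact raised. The documents do not support either. The exposed group is limited to patients never restarted for a non-operative reason, and nothing in the protocol says that they would be more numerous in the cortisone arm.

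Two things remain. First, no passage states that the sentence is an abbreviation, and the Finnish version has no statistical analysis section that could confirm it. The form also collects adverse events of the study drug and the date of stopping, so stops for other reasons are foreseen. A patient never restarted for such a reason would have to be miscoded or left blank. Second, the total pancreatectomy conflict does not depend on how the sentence is read.

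**Conclusion.** The conflict in wording is real and touches the set used for the only non-inferiority test, but a biased exclusion is not shown. The likely intention is that only operative reasons remove a patient, and on that reading the bias is zero. On the literal reading it depends on how many patients are never restarted for other reasons, in which arm, and how badly they do. Over the assumed range (2–5% of the cortisone arm, CCI 20–40 points worse, no loss from pasireotide), the shift is 0.4 to 2.0 points against a margin of 9, and false non-inferiority is about 6–14% instead of 5%. With balanced losses it stays at 5%; with losses only from pasireotide it falls below 5%. This should be fixed before outcomes are examined, because the repair is cheap and removes a choice that could otherwise be made with results in view.

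**What to change.** - Define the modified intention-to-treat set by operative facts only: randomised, pancreatic resection performed, and not judged low-risk at pancreaticoduodenectomy. Reconcile the handling of total pancreatectomy between the English and Finnish lists, and make the analysis-set sentence agree.
- State that a patient whose drug was not restarted, or was stopped, for any other reason stays in the set.
- Add a code to the drug-continuation field for no, other reason.
- Report an analysis of all randomised patients as a sensitivity check. It should support the main analysis and not replace it, because it brings back unresected and low-risk patients, in whom any difference is likely to be diluted.

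The cost is a few sentences in each language version, one form code and one further analysis. The sensitivity analysis needs 30-day CCI for removed patients too. Follow-up already relies on routine care and hospital records, so no extra visits should be needed.

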## **Registration**

The study will be registered in clinicaltrials.gov before recruitment.

## **Data protection**

The collected data and list of patients will be held in locked room and/or electronic data on a computer which is protected with password and encryption.

## **References**

Laaninen M, Sand J, Vasama K, Laukkarinen J. Whipplen leikkauksen jälkeisiä komplikaatioita voidaan vähentää hydrokortisonihoidolla. *Randomoitu*

plasebokontrolloitu tutkimus. Suomen Kirurgiyhdistys ry 2015 36;4

Collected parameters

Name

Social security number

Date of birth

Gender (1 = male, 2 = female)

Charlson comorbidity index

Medication

Anticoagulation (0 = no, 1 = yes)

Immunosuppression (0 = no, 1 = yes)

Cortisone (0 = no, 1 = yes)

Date of diagnosis of pancreatic tumor (suspicion) (=computed tomography date)

Preoperative diagnosis (1 = pancreatic cancer, 2 = cholangiocarcinoma, 3 = IPMN, 4 = NET, etc)

Neoadjuvant therapy (0 = no, 1 = gemcitabine, 2 = folfirinox, 4 = chemoradiotherapy, 4 = other)

Randomization group (1 = signifor, 2 = cortisone)

Date of surgery

Type of surgery (1 = whipple, 2 = distal resection, 3 = enucleation, 4 = median pancreatectomy, 4 = exploration, 5 = total pancreatectomy, 6 = other)

Venous resection (0 = no, 1 = portal/SMV, tangential or end-to-end, 2 = porta/SMV,

Arterial resection (0 = no, 1 = yes)

Pancreaticojejunostomytype (1 = Heidelberg, 2 = [name], 3 = other)

Consistency of pancreas (1 = hard, 2 = soft, normal)

Pancreatic duct at operation (1 = small, normal, 2 = dilated)

Pancreatic duct size, computed tomography, mm

Drains (0 = no, 1 = one drain, 2 = two drains)

Was study drug continued after operation (1 = yes, 2 = no, hard pancreas/dilated duct in patient undergoing whipple, 3 = no, no operation, 4 = no, total pancreatectomy)

Complications, 30 days from operation

Pancreatic fistula, ISGPS grade

DGE, ISGPS grade

Postop haemorrhagia, ISGPS grade

First complication, C-D class

First complication, description (1 = pancreatic fistula, 2 = DGE, 3 = postop haemorrhagia, 4 = pulmonary embolism, 5 = pneumonia, 6 = UTI, 7 = superficial wound infection, 8 = deep wound infection, etcetc)

Second complication, C-D class

Second complication, description (1 = pancreatic fistula, 2 = DGE, 3 = postop haemorrhagia, 4 = pulmonary embolism, 5 = pneumonia, 6 = UTI, 7 = superficial wound infection, 8 = deep wound infection, etcetc)

Third complication, C-D class

Third complication, description (1 = pancreatic fistula, 2 = DGE, 3 = postop haemorrhagia, 4 = pulmonary embolism, 5 = pneumonia, 6 = UTI, 7 = superficial wound infection, 8 = deep wound infection, etcetc)

Fourth complication, C-D class

Fourth complication, description (1 = pancreatic fistula, 2 = DGE, 3 = postop haemorrhagia, 4 = pulmonary embolism, 5 = pneumonia, 6 = UTI, 7 = superficial wound infection, 8 = deep wound infection, etcetc)

Fifth complication, C-D class

Fifth complication, description (1 = pancreatic fistula, 2 = DGE, 3 = postop haemorrhagia, 4 = pulmonary embolism, 5 = pneumonia, 6 = UTI, 7 = superficial wound infection, 8 = deep wound infection, etcetc)

Sixth complication, C-D class

Sixth complication, description (1 = pancreatic fistula, 2 = DGE, 3 = postop haemorrhagia, 4 = pulmonary embolism, 5 = pneumonia, 6 = UTI, 7 = superficial wound infection, 8 = deep wound infection, etcetc)

Postoperative amylase level at day 3

Postoperative drain amylase level at day 3

Postoperative blood sugar level, highest during hospital stay

Date of commencement of normal per oral feeding

Date of discharge

Destination of discharge (1 = home, 2 = primary care ward, 3 = referring hospital)

Referring hospital's name (1 = Helsinki University Hospital, 2 = Lappeenranta, 3 = Lahti, 4 = Kotka, etc)

PAD

Histology (1 = pancreatic ductal adenocarcinoma, 2 = cholangiocarcinoma, 3 = IPMN, 4 = NET, etc)

pT category

pN category

pM category  
Number of examined lymph nodes  
Number of metastatic lymph nodes  
R category

Re-admission, 30 days (0 = ei, 1 = yes)

Reason, free text

Was the blinding unmasked to treating doctors (0 = ei, 1 = yes, inadvertently, 2 = yes, advertently unmasked)

Reason, free text

Date of study drug stopping

Adverse event of study drug (0 = no adverse events, 1 = nausea, 2 = elevated blood sugar, etc)

Postoperative outpatient clinic visit (0 = no, 1 = yes, Helsinki University Hospital)

Adjuvant therapy (0 = no, 1 = gemcitabine, 2 = folfirinox, etcetc)

Date of commencement of adjuvant therapy

Recurrence (0 = no, 1 = local, 2 = liver, 3 = lungs, 4 = peritoneal carcinosis, 5 = multiple)

Date of recurrence

Death (0 = no, 1 = yes, caused by pancreatic tumor, 2 = yes, unrelated to pancreatic tumor, 3 = yes, surgery complication)

Date of death

Last date of follow-up

Remission (0 = no, 1 = yes)

Patient withdrawn consent (0 = no, 1 = yes)

Date of withdrawal

(the study protocol in Finnish)

